### Study from the participants view

After contacting the study administration, the information given to the participants will contain a precise description of the inclusion and exclusion criteria, the structure of the treatment manual as well as the data collection procedure, including the procedure for the videorecordings (Figure 2). Confidentiality of the collected data will be confirmed. Voluntariness of participation will be emphasised by explaining the opportunity to terminate the treatment at every timepoint during treatment and the opportunity to cancel the use of any data collected. Furthermore, an insurance policy for possible negative outcomes resulting from participation in clinical trials will be contracted.

**Figure 2 F2:**
[figure not shown]
Study from the participant’s point of view.

### Statistical analysis

To handle the hierarchical data structures (sessions at level 1 nested within patients at level 2 and therapists at, level 3), a hierarchical linear model (HLM) with time as a within-groups factor and the treatment condition as a between-groups factor will be used for the main research questions [85]. The analyses will be conducted on the intention-to-treat sample as well as on the completer sample. To investigate if patients and therapists have effects on the therapy outcomes, the patients’ and therapists’ pre-treatment characteristics will be investigated as outcome predictors at levels 2 and 3.

### Sample size

Based on a power analysis with G*Power [86], the optimal sample size with an Alpha-error of 5%, a Beta-error of 80% and a correlation coefficient for the repeated assessments of of r = .30 is 60 participants, i.e., 20 participants in each priming condition.

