## Methods/design

This study is a randomised controlled trial with three active treatment arms. This trial will be conducted at the Swiss psychotherapy outpatient clinic in the Department of Psychology at the University of Zürich. Figure 1 depicts the 3 × 4 design with one between-subject factor (resource priming, supportive resource priming, or problem priming) and one within-subject factor (time: pre, mid, post, or follow-up).

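### The sample-size statement gives a beta error of 80%, which is 20% power; 80% power was probably meant, and 60 participants cannot be reproduced from the inputs listed

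*Protocol article*

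**What the plan says.** The Sample size section of the protocol article is a single sentence. It names the software ("Based on a power analysis with G*Power") and then gives the inputs: "the optimal sample size with an Alpha-error of 5%, a Beta-error of 80% and a correlation coefficient for the repeated assessments". The correlation is the only input besides the error rates, and the result follows directly: "of r = .30 is 60 participants, i.e., 20 participants in each priming condition".

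The Methods/design section describes a 3 × 4 layout with three active arms and "one within-subject factor (time: pre, mid, post, or follow-up". The sample-size sentence does not say whether all four waves entered the power analysis, or whether the calculation was for the condition effect, the time effect or their interaction.

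Under Aims of the trial, question 1(a) asks whether the resource conditions reach comparable therapist adherence. Question 3 asks whether they have comparable efficacy on GAD outcomes, general outcomes and dropout, each time against adherence priming.

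**The concern.** Beta is the probability of missing a true effect of the size planned for. Setting it at 80% means accepting an 80% chance of missing that effect, which is four times in five. That is the reverse of the usual convention, and nothing else in the article tells the reader which figure was used. The word power appears only in the phrase naming the power analysis, with no level attached.

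The misprint falls on the quantity that matters most for this trial. Two of the main questions look for similarity between arms. If the arms do not differ significantly, a reader needs to know how large a difference the trial could have detected, and that depends on the type II error and the effect size together. The article misstates the first and does not give the second, so the reader cannot tell what a null result would rule out.

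**Working it through.** **Inputs from the article**
- Alpha 0.05, beta stated as 0.80, correlation r = 0.30, N = 60 as 20:20:20 (Sample size).
- k = 3 arms; four measurement waves in the design (Methods/design).
- Not given: effect size f, tested term, number of waves m entered. These are varied below as assumptions.

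**Step 1: what the stated beta means.** Power = 1 − beta = 1 − 0.80 = 0.20.

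**Step 2: can 60 be reproduced from the stated inputs?** No. Alpha, beta and r do not determine N without f, a tested term and m. What can be done is to fix N = 60 and solve for the f that would make the sentence true under each reading.

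**Step 3: formulas.** Repeated-measures ANOVA, noncentral F, sphericity assumed:
- Condition × time interaction: λ = f²·N·m / (1 − r), with df (k−1)(m−1) and (N−k)(m−1).
- Condition (between) effect: λ = f²·N·m / (1 + (m−1)r), with df k−1 and N−k.

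**Step 4: the f that corresponds to N = 60**

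| Reading (assumed) | Power | λ required | df | f |
|---|---|---|---|---|
| 3×2 interaction | 0.80 | 10.16 | 2, 57 | 0.243 |
| 3×4 interaction | 0.80 | 14.13 | 6, 171 | 0.203 |
| Between factor, four waves | 0.80 | 10.16 | 2, 57 | 0.284 |
| 3×4 interaction | 0.20 | 3.02 | 6, 171 | 0.094 |
| Between factor, four waves | 0.20 | 1.82 | 2, 57 | 0.120 |

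Example for the 3×4 interaction at 80% power: f² = λ(1 − r)/(N·m) = 14.13 × 0.70 / (60 × 4) = 0.0412, so f = 0.203.

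**Step 5: do round values of f point to one calculation?** Sample sizes are taken in multiples of three.
- f = 0.25, 3×2 interaction: λ = 0.0625 × 60 × 2 / 0.70 = 10.71 and power is 0.822 at N = 60. At N = 57 power is 0.7995, so 60 is the first multiple of three to reach 80%.
- f = 0.20, 3×4 interaction: power is 0.786 at N = 60, and 63 are needed for 80%. This is close to 60 but does not reach it.
- f = 0.25, 3×4 interaction: 42 are needed. f = 0.25, between factor with four waves: 78 are needed.
- f = 0.10, 3×3 interaction, literal 20% power: power is 0.205 at N = 60, and 60 is the first multiple of three to reach 20%.

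The first line makes a label swap (power called beta) the likely explanation. The last line shows that the arithmetic alone cannot exclude the literal reading.

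**The case against.** The strongest reply is that this is an evident slip of wording. A conventional f of 0.25 returns exactly 60 at 80% power under one plausible set-up, and nobody would plan deliberately for 20%. If 80% was entered in G*Power, no patient, test or conclusion changes. The article also condenses a fuller protocol that is not shown, and the effect size, tested term and waves may be stated there.

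Much of this stands. The missing effect size is the weaker half of the point and would not be raised by itself. The misstated beta is different: it is an error in the text shown, and an unseen document does not correct what the article prints.

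A reader might go on to infer three stronger things, and the article supports none of them.
- *That 60 is the wrong number.* It fits 80% power under several readings, so the sentence is faulty but the number is not shown to be.
- *That the calculation used two waves, in conflict with the four-wave design.* The match at f = 0.25 with two waves is suggestive, but f of about 0.203 with four waves fits equally well, and the article states neither.
- *That the trial was sized for a difference of about one standard deviation.* Any such conversion needs an f and a pattern of change over time that the article never gives.

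**Conclusion.** The point holds as an error of statement. As printed, the trial has 20% power, and no power level elsewhere in the article corrects this. Power of 80% was probably intended; that is an inference from how well 60 fits, not something the article says.

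The effect for which 60 is adequate ranges from f of about 0.20 to 0.28 across the three 80% readings tabulated, against 0.09 to 0.12 for the two literal 20% readings. All of these assume r = 0.30, alpha 0.05, three equal arms and sphericity, together with a tested term and number of waves that the article leaves open. The sentence therefore cannot be checked as it stands, and a reader cannot tell from it how much a finding of no difference would mean for the comparability questions. The sample size itself is not impugned.

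**What to change.** Check the original G*Power entry. If 80% power was used, replace the beta figure with *power of 80% (beta-error 20%)*. In the same sentence give the effect size f, the term tested (condition, time or their interaction) and the number of waves entered. Keep 60 participants, 20 per condition.

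If the check shows that something other than 80% was entered, report the value actually used.

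The cost is one sentence, with no added patients and no change to the design or analysis. Once the effect size is visible, readers can judge for themselves how far a non-significant result supports comparability.

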### Ethical review

This study protocol is approved by the Ethical Committee of Canton Zurich (KEK 2011–0475) and the Ethical Committee of the Philosophical Faculty of University of Zurich (PhiF-EK_20.1.2012).

## Discussion

Bonafide psychotherapy is an effective treatment for individuals who suffer from GAD and its comorbidities in comparison to no-treatment and treatment as usual [16,17,18]. Rather than creating increasing numbers of new overall treatment-packets within a medical meta-model, an additional approach may be to increase the understanding of already effective psychotherapies [45,48-50]. The psychotherapy field is moving from legitimation and competition focused research to a more comprehension-oriented process-outcome research methodology [47,51]. Treatment manuals and protocols allow a relatively high degree of freedom for the way therapists implement the treatment protocols. The present design experimentally examines the therapists’ within-protocol variability and its relation to treatment outcome. More specifically, three methods of conducting the same treatment protocol are compared to each other using tandem peer-tutoring methodology (resource priming, supportive resource priming, and adherence priming).

The hierarchical structure of the design allows the simultaneous examination of the patients’ contributions and the therapists’ contributions. In contrast to double blinded medication trials, therapists’ and patients’ are informed and actively involved in the psychotherapeutic treatment plans. This involvement is not a bias that has to be eliminated and it might be well an active ingredient of a successful psychotherapy that the therapists’ and patients’ take a proactive, responsive role in the treatment [37,87]. The present design allows for the experimental investigation of some potentially meaningful aspects of this proactive variability.

### Bias minimization

#### Participants

Patients will be randomly assigned to conditions in order to reduce potential biases of participant characteristics. The inclusion and exclusion criteria allow for a relatively homogeneous group of individuals; the primary GAD diagnoses, comorbidities with substance use disorders and severity of depression along with age, sex and gender will be tested as potential confounders.

In traditional psychotherapy trials, where two or more treatments protocols are compared to each other, the patients’ are informed about the various randomised treatment conditions of the active treatments (e.g., psychotherapy vs. waiting list). In the present trial, the patients’ are treated with the same treatment protocol, and, thus the randomisation procedure essentially does not affect the overall treatment plan. Referring to the pre-existing standards, the patients can be blinded to the randomised therapist conditions in order to reduce potential biases from the outcome expectations of the patients.

#### Therapists

A potential bias due to allegiances of the therapists is a concern, especially in human treatments where inductions of outcome expectations can be problematic. To minimise this potential bias, therapists will be allocated to the peer-tutoring partners based on common consent. Furthermore, they will be supervised in mixed groups, where the priming condition plays no explicit role and the supervisors are advised to focus on therapist skills independent of the underlying priming conditions. Nonetheless, because the therapists are informed about the treatment protocol, the allegiances of the therapists to specific CBT protocols will be declared and considered in the statistical analyses.

Keeping the above mentioned strengths and limitations of the present design in mind, the proposed trial addresses the clinically relevant question of how to customise a bonafide psychotherapy using tandem peer-tutoring methodology (three priming conditions). Through the development and testing of the proposed priming procedures, the study could potentially define levels of adherence for conducting an overall treatment protocol more appropriately [52,88].

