**Methods/design:**

This trial will investigate three different methods of customising a bonafide CBT-protocol using dyadic peer-tutoring methodology (primings). The individuals with GAD will be randomly assigned to one of three priming conditions (resource priming, supportive resource priming, or adherence priming). The participant treatment allocation will be performed randomly. Therapists will be assigned to a peer-tutoring partner and priming condition based on a mutual agreement. Treatment outcomes will be assessed at the following times: observer based in-session outcomes, session-by-session post-session outcomes, treatment outcome at post assessment and treatment outcome at 6-month follow-up.

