#### Randomisation and treatment allocation

After meeting the inclusion criteria, patients will be randomly assigned to one of the three conditions (adherence priming, resource priming, or supportive resource priming). Treatment allocation is performed using an online application for full randomisation. In this way, we aim to ensure that the trial arms are balanced with respect to the patients’ baseline characteristics. Randomisation will be conducted by two independent research assistants. Because all patients will be treated using the same CBT-manual, patients are blinded to their treatment allocation and are not informed about the randomisation procedure.

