### Therapists

Twelve advanced trainees with at least 2 years post-graduate training will be recruited from local psychotherapy-training centres. The majority of those therapists have experience as study therapists in a prior randomised controlled trial (ClinicalTrials.gov Identifier: NCT01012856). All of the therapists will participate in an initial 16-hour workshop presented by the (co-)developer of the treatment manual ([name]) [24]. In addition to the peer-tutoring (primings), the therapists will be regularly supervised in small groups on a 14-day basis. The supervision is conducted in mixed groups for all three priming conditions. All of the supervisors also participate in the initial 16-hour workshop. To respect and coordinate the therapists’ preferences (e.g., preferences in working days and time schedules) they will be assigned in a joint face-to-face session at the beginning of the study. All of the therapists will give verbal and written consent for their selected peer-tutoring partner and priming condition. To control for potential effects of particular therapists, we will investigate the therapists’ self-reported interpersonal strengths and problems, their attachment quality and their therapeutic attitudes along with their allegiance to the underlying CBT-protocol.

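### Therapists reach their priming condition by agreement, not by chance; the protocol offers consent-based allocation as a guard against allegiance bias, which it cannot be relied on to be

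*Protocol article*

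**What the plan says.** Patients are randomised to the three conditions (Randomisation and treatment allocation). Therapists are not. The abstract says: "Therapists will be assigned to a peer-tutoring partner and priming condition based on a mutual agreement". The Therapists section of the methods explains that this is meant to accommodate what suits them ("e.g., preferences in working days and time schedules) they will be assigned in a joint face-to-face session at the beginning of the study") and adds: "All of the therapists will give verbal and written consent for their selected peer-tutoring partner and priming condition".

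The Therapists paragraph under Bias minimization raises allegiance as a possible bias and gives the response: "To minimise this potential bias, therapists will be allocated to the peer-tutoring partners based on common consent". It then notes that therapists know the treatment protocol, so that "the allegiances of the therapists to specific CBT protocols will be declared and considered in the statistical analyses". The methods describe the therapist measures as interpersonal strengths and problems, attachment quality and therapeutic attitudes, "along with their allegiance to the underlying CBT-protocol". Supervision is in groups that mix the three conditions, and the analysis is a three-level model with therapists at level 3.

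The Participants paragraph under Bias minimization, however, describes the therapist conditions as randomised.

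**The concern.** The priming acts on the therapist, and the first research questions in Aims of the trial concern what the therapist does: adherence to the protocol and use of resource-activating micro-interventions. Therapists could differ on just these traits before any priming takes place. Randomising patients makes the patients comparable across conditions. It does nothing to make the therapists comparable.

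If the condition is settled by agreement, therapists who already lean towards strengths-based work, or towards close adherence to a manual, may end up in the matching arm. A difference between arms would then be partly a difference between the people in them. For the third question, whether the resource conditions have comparable efficacy, such sorting could either produce a difference or hide one, and its direction cannot be known in advance. The protocol also describes the study as an experimental examination of how therapists carry out the manual, and for the therapist factor that description depends on how therapists come to their condition.

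**Working it through.** The plan gives no figure for therapist variance or for selection, so there is nothing of its own to reproduce. The check has two parts.

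**Reading the sections together**

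1. *Does the agreement cover the condition?* The Bias minimization sentence mentions partners only. The abstract and the Therapists section of the methods both couple partner and priming condition. So the condition is reached by agreement too, but this has to be shown from those two places.
2. *Does each therapist work in one condition?* Both places use the singular for the priming condition, and no section describes a therapist working in more than one. The text never says so outright, and the flow chart is not shown. It is the likely reading, and an inference.
3. *What does the allegiance adjustment address?* Both statements about allegiance refer to the CBT protocol, which is common to the arms ("Because all patients will be treated using the same CBT-manual"). No stated measure is described as covering preference for, or belief in, a priming condition.
4. *Can the other therapist measures stand in?* The interpersonal and attachment scales are taken at the start of the study but are not described as measuring preference for a priming. The Therapeutic Attitude Scale is taken at the overall end of treatment (Table 1, second footnote), so it cannot show attitudes before allocation.

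**Illustrating the size**

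Inputs from the protocol: 12 therapists ("Twelve advanced trainees with at least 2 years post-graduate training will be recruited"), 3 conditions, 60 patients. Assumed: an equal split, partners sharing a condition, a therapist ICC of 0.05 to 0.10, and a selection shift *s* of 0 to 1 therapist SD between two arms.

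- Therapists per arm: 12/3 = 4. Dyads: 12/2 = 6. Patients per therapist: 60/12 = 5.
- Therapist SD in patient-SD units = √ICC: √0.05 = 0.224; √0.10 = 0.316.
- Bias in a between-arm contrast = *s* × √ICC:

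| Shift *s* (therapist SD) | ICC 0.05 | ICC 0.10 |
|---|---|---|
| 0 | 0 | 0 |
| 0.5 | 0.11 | 0.16 |
| 1 | 0.22 | 0.32 |

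The number of patients does not enter this formula, so more patients would not shrink the bias. A level-3 random effect represents variation between therapists around a common mean; it does not remove a systematic shift in which therapists an arm received. With 12 − 3 = 9 therapist-level degrees of freedom for the condition contrast, there is also little room for covariates to absorb it.

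*What random allocation would leave.* With 4 independent therapists per arm, the chance component of a between-arm difference has SE √(2 × ICC/4): 0.16 at ICC 0.05 and 0.22 at ICC 0.10. If partners resembled each other completely, each arm would in effect hold 2 units and the SE would be √(2 × ICC/2), that is 0.22 and 0.32. Chance imbalance can therefore be as large as the illustrated bias. It has expectation zero, however, and can be carried in the standard error.

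**The case against.** The only preferences the protocol names are working days and schedules, and therapists are assigned in a joint session. If timetables decided everything, systematic selection could be close to zero. This stands as far as size goes, and it is why the range above starts at 0. But scheduling is given as an example, and the therapists consent to a condition described as selected.

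A reader might infer that therapists freely choose their arm and that this creates allegiance bias. The documents do not support that. They describe agreement, give no evidence of sorting by belief or skill, and leave room for the argument that consent puts willing therapists in every arm, whereas a draw may place someone in a condition they disfavour. The protocol does not make that argument, and willingness in every arm would not make the arms' therapists alike in skill or strength of belief. What can be said is that the route to bias is open.

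It would also go too far to say that the plan has no safeguard, or that its allegiance measure misses the problem entirely. Mixed supervision, therapist characteristics as level-3 predictors and therapist as a model level all help. Allegiance to CBT can vary between therapists and might be related to a liking for adherence priming. The items of the allegiance self-report are not shown. These safeguards remain partial, since none is stated to measure preference for a priming before allocation.

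Finally, randomising six dyads would not guarantee balance. That is true. The gain is freedom from systematic selection.

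**Conclusion.** The point holds in a limited form. By the protocol's own account, condition is reached by agreement among therapists while only patients are randomised. Offering consent-based allocation as a way to minimise allegiance bias is not sound reasoning, because such allocation may let allegiance influence who works in which arm. On the likely but inferred reading that each therapist works in one condition, the condition contrast is confounded with non-randomly allocated therapists, and the planned safeguards reduce this without removing it.

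The size is unknown. The range of 0 to 0.32 patient SD is an illustration that rests wholly on the assumed ICC (0.05 to 0.10) and shift (0 to 1 therapist SD). It is no estimate, and it does not show that bias has occurred. The description of therapist conditions as randomised, under Bias minimization, Participants, does not fit the abstract or the Therapists section of the methods.

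**What to change.** **If therapists are not yet allocated:** let partners pair by consent, which preserves the scheduling purpose, and then draw the six dyads at random 2:2:2 to the conditions. There are 6!/(2!2!2!) = 720/8 = 90 possible allocations, and one draw at the planned joint session is enough. This turns possible systematic selection into chance error that the therapist level of the model can represent, allowing for any resemblance between partners. The cost is that a therapist may receive a condition they would not have preferred, and that balance is not assured with so few units.

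**If dyads are already allocated:** have each therapist rate preference and expected benefit for each of the three primings, before treatment starts if that is still possible. Use the ratings in a sensitivity analysis alongside CBT allegiance, and state as a limitation that condition effects are confounded with non-randomly allocated therapists. The cost is a short questionnaire for 12 people.

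**In either case:** remove the claim that allocation by consent minimises allegiance bias, say outright whether each therapist works in one condition only, and reconcile the reference to randomised therapist conditions with the allocation procedure actually used.
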